## **5.2 Study Assessments**

Subjects will complete a number of questionnaires.

### **Primary Outcome**

#### **Saturated Fat Intake**

a) Self-reported amount of saturated fat intake will be measured by Margetts et al (1989) 63 item food frequency questionnaire and a two-item self-reported measure. The Margetts, Cade & Osmond (1989) questionnaire is a validated self-report index of food. The frequency of consumption of 63 common foods over the previous month using a 6-point-scale is assessed (two or more times per day; three to five times per week; one to three times per month; rarely or never). The scale has good test-retest reliability ( $r=.61$ ; Armitage & Conner, 1999). In this study a column on reduction on portion sizes will be added and assessed at Time2.

b) Saturated fat intake will be also measured by a two item self perception questionnaire.

#### **c) Portion Size Changes**

Portion size changes in the consumption of 11 high fat items (e.g. meat dishes, whole milk, bacon, cheese ordinary, chocolate, crisps) will be assessed. These items accounted for the highest reported saturated fat intake in the FFQ from a previous study. Participants will be asked to report changes in their portion sizes on a 7 point Likert scale (from 'a lot less' to 'a lot more').

### **Secondary Outcomes**

#### **Other Health Behaviours**

Other health behaviours will be measured by 6 items on a 7 point Likert scale (from 'a lot less' to 'a lot more'). Participants will be asked to report changes in other health areas namely alcohol, use of cholesterol lowering products, weight changes, smoking, physical activity and eating a well balanced diet.

## Self-Efficacy/ Planning/Intentions

There will be a second questionnaire that will cover a range of psychological determinants. The maintenance and recovery self-efficacy, action and coping planning, intentions measures have been adapted from Renner & Schwarzer's (2007) and Schwarzer's (2008) publication on assessment of the Health Action Process Approach Model (HAPA) and from Sienhotta et al.'s (2005) paper on physical activity.

## Reactions to the Intervention

Subjects' opinions of the intervention were adapted from Bourdeaudhuij & Brug (2000), and Brug et al (1998). Two extra items were included on emotional reactions to the information presented ('I felt that the information.....was worrying', ... 'a wake-up call').

### **5.3 Study Duration**

This study requires two online visits to a web site. The same subjects will not be contacted in the future to fill out any other information. The whole process, including screening, main study phase, and follow-up should not last more than 1 hour.

### **5.4 Dispensing and Accountability of Study Supplies**

N/A

### **5.5 Continuation of Treatment**

The study link will be only designed to be used during the study duration. Upon completion of the study, those subjects that are happy will be provided with a link to the Flora website <http://www.florahearts.co.uk/Consumer/Home.aspx> and will be given the opportunity to test their Heart-Ages and sign up to a free Health Plan. Subjects will be provided with instructions by Virtual Surveys on how to get the free health plan once they visit the website.

## **6. Premature Withdrawal**

### **6.1 Withdrawal from the Study**

If a subject meets the inclusion criteria but decides to withdraw mid-way through the study then no data will be uploaded in the system and a request will be made to virtual surveys for this person to be replaced by another subject with the same characteristics.

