## 1.3 Brief Description of Intervention

To the best of our knowledge there are no studies that have tested online the combined effects of planning with SMS reminders in a more complex behaviour such as dietary changes. In the present study, the aim was to test for differences on the effects of three different conditions on saturated fat intake and the purchase of products that contribute to lowering or helping maintain a healthy diet.

At **Time 1**, subjects will be invited to participate in the study by an online recruitment agency, which will also carry out the screening process. Once, subjects have been accepted in the study they will be randomly allocated into one of three conditions. In the most advanced condition, subjects will be asked to form implementation intentions and be reminded of their plans by SMS reminders over the course of the two weeks. In the second condition, they will be asked to form plans on how to eat healthier over the course of two weeks. All conditions will be asked to fill out questionnaires on: a) a self-reported dietary intake questionnaire (Margetts et al, 1989) and b) a self-reported questionnaire on various social cognitive variables (e.g. intentions, self-efficacy). The Control Group (CG) will be only asked to fill out these questionnaires at this stage. All three groups will receive educational information on the importance of a healthy diet low in saturated fat and the association between high cholesterol and being overweight. A coupon of a cholesterol lowering product, with 50p off the face value, will be posted to all participants as a reward for successfully completing baseline assessments.

At **Time 2 (4 weeks later)**, subjects will be invited to fill out again the same dietary measures of food intake and an extension of the psychological determinants' questionnaire. Study subjects will be rewarded for their participation in the study (£15). This will be upon completion of study phase 2.

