### **6.2 Consequences of Missing Assessments**

There are two assessment points in this study. Virtual Survey has suggested a 30% drop out from one study phase into the next. To account for this, more than 725 subjects will be recruited to end up with roughly 500 subjects at Time2.

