### **9.4. Data Protection**

Information relating to this study will be kept confidential and the subjects' right to check personal data will be fully protected in accordance with the Data Protection Act 1998. Use of Case Record Forms is not applicable in this study since all information will be gathered via an online system. Each subject will be allocated with a unique ID at the recruitment stage (by Virtual Surveys) which will remain the same until the end of the study. Subjects will be responsible for entering their data on the system and no personal details such as (first name, last name and email addresses will be asked of the subjects). Subjects will be though required to fill out some personal health information, gender, date of birth, mobile number to receive feedback at the end of the study. To secure any personal information, data such as mobile numbers will be stored by a third party to Unilever into a different database with a higher level of security. This data will be deleted upon participants' study completion. Participants will also be informed that their mobile numbers will be only used during the duration of the study and will be deleted upon completion of the study.

The subject may choose not to provide certain information, but this may mean they will not be able to complete the study and their data will be replaced by new participant data. The site will not contact the user and Unilever Discover will not knowingly sell, rent, or trade the personal information collected.

All web-based interaction data (apart from mobile numbers) will be stored for a period of five years in a secure central database hosted by Unilever. Only a few project members will have access to this folder. Data files on the mainframe will be backed-up automatically. All data files will be backed-up and stored in a secure location.

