### **3.5 Final report**

A summary will be issued within four weeks of study completion and a final report within 4 weeks of sponsor's comments. This report should include number of subjects enrolled, number of subjects dropped/withdrawn, deviations, amendments, statistical analysis and general or specific comments from the investigator. Additionally, the contract laboratory will provide the sponsor/study co-ordinator with the electronic data.

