**NEXT**

**APPENDIX 5: Recruitment Agency Screening**  
**Health Check Survey: Draft Questionnaire v1**  
**2417 – Email Invite**

**Invite : Stage 1**

From xxxxxx xxxxxx

Subject: Help us with our research

---

Dear panel member,

Today, we are inviting you to take part in a Health Check survey focusing on healthy eating for a healthier cholesterol level. **This will involve interacting with the system at two times over a period of four weeks.** The first time will not take more than 30 minutes. All those eligible and completing all two different interactions will be paid <<pointsAsMoney>>

Instructions on how to take part can be found below. We look forward to hearing your opinions.

The full research programme will run until <<end\_date>>. You can take part in the first stage until <<end\_date>>. Please note this research project is limited to 725 respondents. Once 725 suitable respondents have completed the survey the project will be closed.

XXXX XXXX

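### The discard-and-replace rules in Protocol 6.1 and 9.4 are not limited to losses before random allocation, so as written they can remove randomised subjects and their data

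*Protocol*

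**What the plan says.** Two places provide for replacement.

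- **Protocol 6.1.** If someone who meets the inclusion criteria withdraws part-way, "then no data will be uploaded in the system and a request will be made to virtual surveys for this person to be replaced". The substitute is to be another subject "replaced by another subject with the same characteristics".
- **Protocol 9.4.** A subject may decline to give certain information, but "this may mean they will not be able to complete the study and their data will be replaced by new participant data".

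Two places deal with losses by over-recruitment and do not mention replacement.

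- **Protocol 4.1** recruits 750 at Time 1 to allow for drop-out.
- **Protocol 6.2** expects "a 30% drop out from one study phase into the next" and recruits more than 725 so that roughly 500 remain at Time 2.

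On timing, Protocol 1.3 says that once "subjects have been accepted in the study they will be randomly allocated into one of three conditions", all at Time 1. The Stage 1 invitation in Appendix 5 adds a closing rule: "Once 725 suitable respondents have completed the survey the project will be closed". Part III, 3.5 asks the final report for the "number of subjects dropped/withdrawn", without asking for it by arm.

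**The concern.** Replacing someone who stops before allocation does no harm. Replacing someone who stops after it changes who is compared, because membership of the analysed arm then depends on something that happened after randomisation. The arms differ in what they ask of people: questionnaires only, a planning task, or a planning task followed by two text messages a week. Withdrawal could therefore depend on arm. It could also depend on motivation, which Protocol 4.1 itself treats as bearing on whether plans work.

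Matching the substitute on recorded characteristics does not repair this, since the substitute too is kept only by not withdrawing. If the substitute were placed directly in the vacated arm, that person would not have been randomised at all; the protocol does not say which route applies.

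The matter cannot simply be left to a statistical analysis plan. Data that were never uploaded cannot be brought into an analysis of all randomised subjects, nor used to compare withdrawers with completers in each arm.

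**Working it through.** **1. The plan's own figure.** Inputs: more than 725 recruited and 30% drop-out (6.2).

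725 × (1 − 0.30) = 507.5, which reproduces the roughly 500 in 6.2. With the 750 of 4.1, 750 × 0.70 = 525. Over-recruitment alone reaches the target, so replacement is not needed.

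**2. Do the two approaches fit together?** Suppose every lost subject were replaced until 725 had complete data. At 30% loss, 725 / 0.70 ≈ 1,036 would have to be allocated, and about 311 of them would leave no data. Nothing in 6.2 envisages this, and its fall from 725 to about 500 presupposes no replacement. So 6.2 and 6.1 either govern different losses, without saying which, or contradict each other.

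**3. Where the rules fall relative to allocation.**

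| Place | Order |
|---|---|
| Part I schematic | Screening, consent, questionnaires, then allocation, all in Phase 1 |
| 1.3 | Allocation once accepted, at Time 1 |
| 5.1(b) | Allocation, then the planning task, then SMS over four weeks |
| Appendix 1 | Allocation listed ahead of the Time 1 questionnaire |

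On every ordering the planning task and the SMS period come after allocation. Stopping mid-way therefore includes stopping after randomisation, and neither 6.1 nor 9.4 excludes that case.

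**4. How much could it matter?** The protocol gives no rate for 6.1 withdrawals, so this step rests on assumptions:

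- no true effect, and an outcome scaled to SD 1;
- equal allocation (the ratio is not stated), so 500 / 3 ≈ 167 analysed per arm;
- uninformative loss in the control arm;
- in one active arm, a proportion *w* withdraws, with withdrawal linked to outcome by correlation ρ between 0.1 and 0.5.

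Bias = ρ × φ(z_w) / (1 − w), where z_w is the *w* quantile of the standard normal and φ its density.

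SE = √(2/167) = 0.109.

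Type I error = P(Z > 1.96 − bias/SE) + P(Z < −1.96 − bias/SE).

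Example with w = 0.10 and ρ = 0.5: z_w = −1.282, φ = 0.1755, bias = 0.5 × 0.1755 / 0.90 = 0.097, bias/SE = 0.89, type I error = 14.5%.

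| w | ρ | Bias (SD) | Two-sided type I error |
|---|---|---|---|
| 5% | 0.1 | 0.011 | 5.1% |
| 5% | 0.5 | 0.054 | 7.9% |
| 10% | 0.1 | 0.019 | 5.4% |
| 10% | 0.5 | 0.097 | 14.5% |

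**The case against.** The best defence is that 6.1 may touch few people. Its wording fits someone who abandons the online session before allocation, where replacement is harmless. The 30% non-return is dealt with in 6.2, and Protocol 11.1 says participants are randomly allocated, which could cover replacements too. Subject IDs are assigned at recruitment, the agency keeps an enrolment log, and each withdrawal triggers a replacement request, so withdrawals could be counted. Imputation and sensitivity analyses belong to the statistical analysis plan promised in 11.2. Finally, the bias in the illustration is that of any analysis leaving out informative withdrawers, replaced or not.

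Most of this is fair, and it rules out several stronger readings that a reader might infer:

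- **That the 30% drop-out measures the harm.** If 30% of one active arm were lost in the way assumed above, the bias would be 0.05 to 0.25 SD and the type I error 7.4% to 62%. But 6.2 handles that loss by over-recruitment, so these figures do not describe the 6.1 rule.
- **That the bias must favour the intervention.** Waiting-list controls could leave more often than active subjects, and all arms are paid only after Stage 2.
- **That substitutes are hand-picked into an arm.** Their route of allocation is simply not stated.
- **That 9.4 deletes records for any blank item.** It applies only where the missing information prevents completion.
- **That the rule conflicts with Part III, 3.5.** A withdrawal can be counted without outcome data; what is missing is a count by arm.

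What survives is that the text draws no line at allocation, and that data not captured cannot be recovered by any later plan.

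**Conclusion.** The point holds in this limited form. As written, 6.1 and 9.4 permit the removal and replacement of randomised subjects because of a post-allocation event. They leave the substitute's allocation undefined and are not reconciled with 4.1 and 6.2. The rule compromises the randomised comparison to an extent that the documents do not allow anyone to measure. Under the stated assumptions the bias runs from about 0.01 to 0.10 SD, and the type I error from barely above 5% to about 15%, for 5% to 10% informative withdrawal in one active arm. If 6.1 withdrawals are rare or unrelated to outcome, the effect is negligible.

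The case for changing the text does not depend on the upper end of that range. The rule serves no purpose that over-recruitment does not already serve, and it discards the information needed to tell whether harm was done. It should be settled before recruitment starts.

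**What to change.** - **6.1 and 9.4:** restrict replacement to subjects who stop before allocation. After allocation, make no replacement; keep the allocation, the data already entered and the point of withdrawal, unless the subject asks for erasure.
- **4.1, 6.2 and the Appendix 5 invitation:** count the 725 or 750 as randomised subjects, not as people who have completed the survey, and state that over-recruitment is the only provision for losses after allocation.
- **11.4:** define the analysis population as all randomised subjects in the arm assigned. The handling of missing Time 2 values can stay with the statistical analysis plan. Carrying baseline forward would not apply directly to portion-size change, which is measured only once, at the end.
- **Part III, 3.5:** report withdrawals and non-return by arm.

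**Cost:** a few sentences of protocol text, a system that saves partial records, and a check that the consent wording covers keeping data already entered. Somewhat more missing Time 2 data will have to be handled, which the over-recruitment already allows for. Keeping baseline records does not supply the missing Time 2 answers, so some bias may remain, but it can then be examined.

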### **6.2 Consequences of Missing Assessments**

There are two assessment points in this study. Virtual Survey has suggested a 30% drop out from one study phase into the next. To account for this, more than 725 subjects will be recruited to end up with roughly 500 subjects at Time2.

## **7. Investigational Events**

### **7.1 Endpoints**

#### **7.1.1 Primary**

The primary endpoint is:

- a) Self-Reported Saturated Fat Intake
- b) Portion Size Changes

#### **7.1.2 Secondary**

The secondary endpoints are:

- a) Other health behaviours
- b) Intention to reduce saturated fat intake
- c) Maintenance and recovery self-efficacy
- d) Action and coping planning

e) Reaction to the intervention

## **8. Experimental evaluations**

### **8.1 Biological Samples**

No biological samples are being collected in this study and there are no invasive measures.

## **9. Safety**

Subjects will be recruited only when the appropriate approvals have been granted.

### **9.1. Unilever Safety Clearance Requirements**

N/A

### **9.2. Local Research Ethical Review Requirement**

The authorised protocol and other appropriate documentation will be subject to the approval of Colworth Research Ethics Committee. The study will not proceed without the written approval of the Ethics Committee and any recommendations for change or additions will be discussed and necessary changes made. Finally the Research Ethics Committee will be sent a summary of the study findings for their information.

### **9.3. No Fault compensation**

In the unlikely event of any subject suffering any significant deterioration in health or wellbeing arising as a result of taking part in this study, Unilever has undertaken to compensate them without having to prove that anyone involved in this study has been negligent. Any dispute will be referred to an arbitrator.

### **9.4. Data Protection**

Information relating to this study will be kept confidential and the subjects' right to check personal data will be fully protected in accordance with the Data Protection Act 1998. Use of Case Record Forms is not applicable in this study since all information will be gathered via an online system. Each subject will be allocated with a unique ID at the recruitment stage (by Virtual Surveys) which will remain the same until the end of the study. Subjects will be responsible for entering their data on the system and no personal details such as (first name, last name and email addresses will be asked of the subjects). Subjects will be though required to fill out some personal health information, gender, date of birth, mobile number to receive feedback at the end of the study. To secure any personal information, data such as mobile numbers will be stored by a third party to Unilever into a different database with a higher level of security. This data will be deleted upon participants' study completion. Participants will also be informed that their mobile numbers will be only used during the duration of the study and will be deleted upon completion of the study.

The subject may choose not to provide certain information, but this may mean they will not be able to complete the study and their data will be replaced by new participant data. The site will not contact the user and Unilever Discover will not knowingly sell, rent, or trade the personal information collected.

All web-based interaction data (apart from mobile numbers) will be stored for a period of five years in a secure central database hosted by Unilever. Only a few project members will have access to this folder. Data files on the mainframe will be backed-up automatically. All data files will be backed-up and stored in a secure location.

### **9.5 COSHH**

N/A

### **9.6 Head of Research**

Once all of the study approvals have been collected, the Corporate Clearance form will be signed off by the Head of Corporate Research.

## **9.7 Microbiology**

N/A

## **10. Serious Adverse Events**

Any adverse event that is considered SERIOUS must be reported within one working day by the investigator to the sponsor/study co-ordinator (for definition see Protocol part III; section 2.5 “Adverse Event”).

## **11. Statistical Considerations**

### **11.1 Description of Statistical methods and interim analysis**

This is a randomised, stratified, between-groups study with the factors 'Planning' and 'SMS Reminders'. The primary endpoint is the change in saturated fat and portion size changes in participants allocated to the three different experimental conditions (Planning, Planning and SMS Reminders and Control Group). Participants will be randomly allocated to one of these three conditions, stratifying for age group (30-45 years or 46-60 years) and gender. Self-reported portion size changes will be measured at a single point at the end of the study. Participants' saturated fat intake will be measured at baseline and upon completion of the study (2 weeks after enrolment). The statistical analysis will compare the efficacy of the three treatment groups via the change in saturated fat intake between the baseline and final diet assessments and change in portion sizes at the end of the study. There will be no interim analyses.

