## **2. Study Objectives**

### **2.1 Primary Objectives**

#### **Objectives:**

The primary aim of the present study is to test the effects of Planning and SMS Reminders on saturated fat intake and purchase of a healthy product over a period of two weeks.

To assess the above, three questionnaires will be issued:

1. Margetts et al (1989) food frequency questionnaire
2. A two item self-reported saturated fat intake measure
3. Self-reported changes in portion sizes

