## **3. Study Design**

### **3.1. Design and Rationale**

This is a randomised, stratified between-groups study designed to assess the difference in saturated fat intake and coupon up-take between the three different experimental conditions; a) Planning and SMS reminders, b) Planning and c) Control Group. Subjects will be randomly allocated to one of these conditions and their responses will be measured by self-reported questionnaires.

Allocation to the subjects in the conditions will be stratified to balance by age group (30-45 years or 46-60 years), and gender. To help minimise any other imbalance effects obese (BMI $\geq$ 30) and non-obese participants (BMI $\geq$ 25), smokers and non-smokers will be also evenly allocated across the different cells.

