### **11.2 Data Analysis and Plan of Efficacy**

A full statistical analysis plan will be formulated in collaboration with [name] from the Unilever Statistics Group, Colworth Park. The effect of the design factors will be determined by comparing the proportion of subjects who have reduced their self-perceived saturated fat intake. Analysis of variance with baseline covariates will be conducted to analyse the behavioural (TIS, FFQ, portion sizes changes, other health behaviours) and social-cognitive measures (intentions, self-efficacy, planning, feedback). Baseline self-reported saturated fat intake will be included as a covariate for the analysis of the primary outcome measures. The stratification variables will be included in the models as will other covariates found significant at the 0.05 level. Comparisons between treatments will all be reported using two-sided significance levels (i.e. making no prior assumption about which treatment group will be most effective). Separate analysis of the effects of modifiers and mediators will be conducted in order to gain a better insight as to who benefits from the intervention.

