### **11.3 Sample size and power determination**

The primary endpoint of self-perceived SAFA intake reduction will be assessed using analysis of variance with baseline covariates. Data from a previous study indicates that around 180 respondents should be sufficient to give power 0.8 of seeing a significant difference (at the two-sided 0.05 level) between the control and planning groups for this endpoint. No prior data exists for the portion size change measure.

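### The primary endpoint is defined inconsistently: most sections make saturated fat and portion size primary, 11.3 powers only self-perceived intake, and purchase or coupon up-take is an aim with no stated endpoint or collection method.

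*Protocol*

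**What the plan says.** - **Summary.** The primary endpoint is saturated fat intake by the food frequency questionnaire (FFQ), together with portion size changes.
- **2.1.** The primary aim covers saturated fat intake and purchase of a healthy product. It continues: "To assess the above, three questionnaires will be issued". The three are the FFQ, a two-item saturated fat measure and portion size changes.
- **3.1.** The design is meant to assess "the difference in saturated fat intake and coupon up-take between the three different experimental conditions".
- **5.2, Primary Outcome.** Saturated fat is measured by a "63 item food frequency questionnaire and a two-item self-reported measure", and portion size changes stand under the same heading.
- **7.1.1 and 11.1.** Both name saturated fat and portion size under one primary endpoint. Section 11.1 reads: "The primary endpoint is the change in saturated fat and portion size changes in participants allocated to the three different experimental conditions".
- **11.2.** The effect of the design factors is judged by the share of participants whose self-perceived intake fell. Analysis of variance is also planned for the behavioural measures. The section refers to primary outcome measures in the plural, defers to a full SAP, and adds: "Comparisons between treatments will all be reported using two-sided significance levels".
- **11.3.** The primary endpoint is the reduction in self-perceived intake, analysed by analysis of variance. About 180 respondents are said to give power 0.8 for a "significant difference (at the two-sided 0.05 level) between the control and planning groups for this endpoint". The section adds: "No prior data exists for the portion size change measure".

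**The concern.** A trial needs one statement, fixed in advance, of what decides it. Here the sections give different answers on three points:

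- which measure is primary;
- how the powered measure is analysed, as a proportion or as a mean;
- whether purchase is part of the primary question.

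Section 1.2 says the effects on saturated fat in the previous study were quite small. With small effects, several candidate measures can easily disagree, and the conclusion then depends on which of them is called primary. If that choice is open when the data arrive, the nominal error rate no longer describes the claim, and the power statement may not refer to the measure being reported. An outcome that is not collected cannot be restored by any later analysis document.

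**Working it through.** **Step 1. What each section makes primary.**

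| Place | FFQ | Two-item score | Portion size | Purchase or coupon |
|---|---|---|---|---|
| Summary | yes | no | yes | no |
| 2.1 | yes | yes | yes | named, no instrument |
| 3.1 | saturated fat, instrument not named | (same) | no | coupon up-take |
| 5.2 | yes | yes | yes | no |
| 7.1.1, 11.1 | saturated fat, instrument not named | (same) | yes | no |
| 11.3 | no | yes | no | no |

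Reading 11.3 as the two-item score is an inference, but a firm one. Section 5.2 calls the two-item instrument a self-perception questionnaire, and Appendix 3 lists it under perceptions of saturated fat intake. The summary therefore names one instrument and 11.3 powers another.

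**Step 2. Purchase and coupon up-take.** Section 1.3 says a coupon is posted to all participants. Neither outcome appears in 7.1.1, 7.1.2, 5.2 or Appendix 3. The nearest item is self-reported use of cholesterol-lowering products, which belongs to the secondary outcomes and measures use, not purchase.

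**Step 3. The plan's own figures.** The attrition arithmetic in 6.2 holds: 725 × 0.7 = 507.5, or roughly 500. The 180 cannot be reproduced, because no effect size or SD is given and the text does not say whether it is per arm. Solving d = (1.960 + 0.842) × √(2/n) for the effect it implies, and taking 500/3 ≈ 167 completers per arm:

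| Reading of 180 | n per arm | Implied d | Power at 0.05 | Power at 0.05/9 |
|---|---|---|---|---|
| Per arm | 180 | 0.295 | 77% | 47% |
| Total, two arms | 90 | 0.418 | 97% | 85% |
| Total, three arms | 60 | 0.511 | 99.7% | 97% |

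These apply only to the self-perceived score and only to Control versus Planning. Nothing comparable can be computed for the FFQ or portion size.

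**Step 4. Size of the multiplicity, if nothing controls it.** Inputs: three arms (three pairwise contrasts), three measures, two-sided 0.05, no true effects, equal arms. The correlation between measures is not in the protocol, so it is an assumption and is varied. The simulation used 1,000,000 replicates, with the shared arms built in.

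| Assumed correlation | Nine unadjusted tests | Pairwise tests only after a significant overall ANOVA |
|---|---|---|
| 0 | 32.3% | 14.2% |
| 0.3 | 31.0% | 13.7% |
| 0.5 | 28.5% | 12.7% |
| 0.7 | 24.9% | 11.1% |
| 0.9 | 19.6% | 8.5% |

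One measure with three unadjusted contrasts gives 12.2%. One measure with one contrast gives 5%.

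Two checks by hand at correlation 0: 1 − (1 − 0.122)³ = 0.323, and 1 − 0.95³ = 0.143. Treating all nine tests as independent would give 1 − 0.95⁹ = 0.370, which is too high because the contrasts share arms.

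**The case against.** The summary and sections 5.2, 7.1.1 and 11.1 agree on saturated fat plus portion size, and 11.3 does name one endpoint and one powered contrast. That stands. The fault is a conflict between 11.3 and those sections, with 2.1 and 3.1 adding a further aim. It is not that every section says something different.

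Multiplicity and the order of contrasts commonly belong in the SAP, and 11.2 defers to one. That also stands. A reader might infer that all nine comparisons are tested at 0.05 and that the trial therefore carries a false-positive risk of 25% to 32%. The protocol does not say so. Section 11.2 fixes sidedness, not level, and its only 0.05 concerns which extra covariates are kept. The 0.05 in 11.3 belongs to one contrast on one endpoint. The protocol states neither an adjustment nor its absence, and the planned analysis of variance could act as a gate.

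A reader might also infer that coupon redemption is not tracked. The protocol is silent on this, so the supportable statement is that no collection method is given.

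The two-factor wording in 11.1 is minor. The same section lists three conditions, and the effect of adding SMS can still be estimated as Planning and SMS versus Planning.

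What the objection does not remove is the contradiction. Whichever endpoint a SAP chose, it would overrule some section of the protocol.

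**Conclusion.** The concern holds as an inconsistency in the protocol's own text, and this part needs no assumption about significance levels. Several measures are called primary with no hierarchy or combining rule. The power statement covers only one of them, that one has two competing analyses, and purchase or coupon up-take is an aim with no listed endpoint or stated means of collection.

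The error rates are conditional. Without any control over nine tests the family-wise error is about 20% to 32%, for assumed correlations from 0.9 down to 0. Behind an overall ANOVA it is 11% to 14% for correlations from 0.7 down to 0, and lower still at 0.9. If the single endpoint of 11.3 is taken with three unadjusted contrasts it is 12%. Which of these applies, if any, depends on a SAP that is not shown, so none should be quoted as the trial's actual risk.

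It may also be tempting to conclude that the protocol must impose a fixed sequence, with Planning versus Control first. The documents do not support that. Section 1.2 asks whether the combination does better than planning alone or than control, and section 1.1 cites a study in which the combination was superior while plans alone were not effective. Such a gate could block the question the trial was set up to answer.

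**What to change.** 1. In the summary and sections 2.1, 5.2, 7.1.1, 11.1 and 11.2, name one primary endpoint: the two-item self-perceived saturated fat score on which 11.3 is powered.
2. State one primary analysis for it: analysis of variance with the baseline score as covariate. Make the proportion who reduced intake supportive.
3. List the FFQ and portion size changes as secondary.
4. Remove purchase and coupon up-take from 2.1 and 3.1 (and the matching aim in 1.3), or demote them to exploratory with a stated method of collection. If the existing item on cholesterol-lowering products is used, say that it measures use and not purchase.
5. In 11.1, describe arm as one three-level factor, since there is no SMS-only group.
6. Leave the order of contrasts and the multiplicity method to the SAP.

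The cost is protocol wording. The downside is that FFQ and portion-size results become secondary, so the main claim rests on a two-item self-perception score rather than on the questionnaire that 5.2 describes as validated. If the sponsor would rather keep the FFQ as primary, the power statement in 11.3 would have to be redone for it, with an effect size and SD.
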